## Abstract

**Background:**

In Canada, a majority of children and adults are insufficiently active for health gains, and about one in seven children and over 20% of adults are overweight or obese. Overweight and obesity are risk factors for many chronic diseases in both adults and children and can result in lower quality and quantity of life. Children whose parents are overweight or obese are more likely to become overweight themselves. Thus, parent/child interventions are important for reducing obesity and promoting long-term healthy weights among members of the family unit. Programs using Co-Active coaching have resulted in positive behaviour changes among adults with overweight/obesity; however, little research has explored the effects of Co-Active coaching on parents, and the consequent impact on the family unit (i.e. all parents and children in the same household). This protocol paper provides a detailed methodological account of a coaching-based program targeting parent and child dyads, in hopes of enhancing health behaviours within the family unit.

**Methods:**

Using a randomized controlled trial design, the researchers aim to identify the impact of coaching plus education (intervention) compared to education only (control) on parents with overweight/obesity and their children (ages 2.5–10, of any weight). A total of 50 dyads are being recruited and randomly assigned using a 1:1 ratio into the control or intervention group. The control group receive 6 webinar-based education sessions focused on physical activity and nutrition. The intervention group receive the same education sessions and nine, 20-min telephone-based sessions with a certified coach. Coaching and health education sessions are conducted with the parent/guardian of the dyad. This paper provides a detailed methodological account of this program.

**Discussion:**

The expected findings from this research will advance coaching literature, research, and practice on this topic by determining whether coaching and education are more effective than education alone at producing behaviour changes among a family unit. If proven effective, this approach may be applied more broadly through public health interventionists to parent and child populations in hopes of affecting change with both individuals and their families.

**Trial registration:**

ISRCTN ISRCTN69091372. Retrospectively registered 24 September 2018.

## Background

Currently, fewer than 10% of Canadian children meet the guideline of 60 min of moderate-to-vigorous physical activity (MVPA) per day, while only 15% of Canadian adults meet the guideline of 150 min of MVPA per week [1]. In addition, it has been reported that Canadian adults with children are less active than those without children [1]. Long-term persistence of these behaviours can result in the development of overweight/obesity in both adults and children, in turn causing the development of adverse health conditions, which are generally preventable [2, 3]. Overweight/obesity in early life stages continues into adolescence and adulthood, and can result in lifelong struggles with physical, mental, and social health (e.g., asthma, blood pressure, weight-based stigmatization, behavioural problems, and low self-esteem [3–5]).

Family and home environments shape early health habits, and parents play a crucial role in developing their children’s nutrition and physical activity (PA) behaviours, in that parents determine the types of foods available in their homes and provide opportunities to be active (or inactive [6]). Therefore, it is important to encourage and support the development of healthy behaviours within the family unit, and to provide parents with resources and knowledge to promote these healthy habits.

Interventions designed to prevent and/or reduce obesity in adults and children, should engage both parent and child in order to develop healthy behaviours within the family unit overall. Thus, the researchers of this project sought to determine the impact of coaching and/or education on parents with overweight/obesity and the consequent impact on their children (aged 2.5–10, of any weight).

### Pediatric and adult overweight/obesity and associated adverse effects

#### Pediatric overweight/obesity

American data reveals that one quarter of preschool-aged children have overweight or obesity; in Canada, 8.5% of children aged 5–9 years and 12.9% of 10–14 year-olds experience obesity [7, 8]. In the same age groups, the rates of overweight are 15.4% (5–9 year-olds), and 23.0% (10–14 year-olds [8]). Males aged 5–11 were reported as significantly more likely to have obesity than females in the same age group [9, 10]. These are alarming statistics for a problem that is preventable if supportive and sustainable lifestyle tools are in place.

The increase in obesity rates also has caused a drastic increase in the incidence of adult obesity-related diseases, such as Type 2 diabetes, cardiovascular disease (CVD), obstructive sleep apnea, and mental disorders in children [11]. Children with overweight/obesity are more likely to develop CVD compared to adults, and subsequent weight loss may not eliminate that excess risk [5]. Conditions such as elevated blood pressure, insulin resistance, and dyslipidemia (i.e., an abnormal amount of lipids in the blood) are being diagnosed in children, prompting the growth of new specialties and clinics targeted toward treating hypertension, Type 2 diabetes, and fatty liver in pediatric populations [5]. Children with obesity are 3 times more likely to develop hypertension than their normal-weight counterparts, and 40% of children with overweight will continue to have increased weight during adolescence [3]. In fact, up to 80% of adolescents with obesity will maintain this weight status into adulthood [3].

Obesity is related significantly to feelings of shame in children, which may affect the development of the child’s personality, identity, and socialization, and can result in decreased pursuits of higher education [12]. A review conducted by Hamilton and colleagues [13] outlined that, in the United States, 25 to 31-year-old adults who experienced obesity as adolescents earned 7.5% less than their counterparts who did not have obesity as adolescents. Lifetime healthcare costs and income penalties were greater in females who experienced obesity as adolescents, while costs due to workdays lost were greater in males who experienced obesity as adolescents [13]. In addition, there seemed to be proportionality between BMI and costs, in that lifetime costs (i.e. healthcare costs and productivity loss costs) increased in proportion with excess weight in childhood or adolescence [13].

The above overview underscores the intensity of overweight/obesity-related issues for children, and the importance of encouraging and developing early healthy bodyweight behaviours among children of any weight [14, 15]. As outlined below, parents’ own obesity status and behavioural prompts are key influencers in the development of their children’s healthy behaviours.

#### Adult overweight/obesity

In 2014, 20.2% of Canadians 18 and older (roughly 5.3 million adults) reported height and weight that classified them as obese, and 40.0% of men and 27.5% of women were classified as overweight [10]. Similar to childhood overweight/obesity, the condition in adulthood is a risk factor for developing poorer health outcomes such as diabetes, heart disease, stroke, and some types of cancer [16]. The psychological effects of obesity are among the most underestimated consequences of this disease; these include reduced quality of life, bullying, negative self-esteem, increased anxiety, risk of isolation, and worsening depression [12].

The causes of obesity are complex, and include an interaction of biology/genetics, behavioural, social, and environmental factors that result in excess weight [17]. In order to encourage sustainable healthy behaviour changes, it is important to implement lifestyle interventions that address a variety of risk factors [17].

### Importance of involving parents in childhood obesity prevention/interventions

Dietary and PA habits established during the early years determine the progression of obesity later in life [18], Given children’s parents, home, and family environments are among the strongest influences on their health behaviours, an optimal method for promoting and encouraging positive behaviour change is targeting, as a dyad, parents *and* their children during their formative younger years [18–21].

The odds of becoming obese as an adult are doubled for children under age 10 who have at least one obese parent, and the probability of childhood obesity persisting into adulthood is estimated to increase from approximately 20% at age 4 years to approximately 80% by adolescence [22]. Therefore, interventions that require only the adult dyad member to be overweight or obese provide a suitable approach.

Children’s obesity-related behaviours are influenced by parental knowledge (how to cook healthy meals), attitudes (valuing PA), modeling (being active themselves), support (financial, logistical, participating with their child), and encouragement [1, 23–26]. In fact, parental role modeling and support for PA are independently associated with their children’s PA levels [1]. Furthermore, when compared to interventions targeting children only, programs that also engage parents are associated with higher self-esteem among the children participants [27].

Previous research examining the influence of family on childhood overweight/ obesity has focused predominantly on parent-centered, unidirectional aspects of parenting (i.e., what the parent does or believes), including maternal feeding practices, and parental PA and nutrition knowledge [6]. Specifically, childhood obesity researchers have measured primarily characteristics and/or behaviours of the parent and child individually [18]. More recently, researchers have examined parents’ actions as well as how they complete these actions, by investigating relationships between parenting styles and young children’s weight status [18]. The direction of developmental research has also shifted to viewing the parent and child as a unit or dyad as opposed to as individuals, thereby examining and encouraging an interactive perspective on the parent-child relationship [18, 28]. This interactive standpoint reflects the relations between parents and their children and demonstrates that children’s development is shaped by the reciprocal nature of both parent- and child-level factors [18, 28].

A further reason to communicate with parents about their children’s health behaviours is to increase parental awareness regarding the risks associated with children developing overweight/obesity and its adverse conditions, and to encourage parents to take action toward promoting healthy behaviours [29]. Parents who recognize excess weight in their children as a health risk may be more motivated to encourage healthy behaviour change than parents who do not [30, 31]. Thus, education and support for parents is a fundamental step to promoting healthy behaviours in children and their families [21].

Although child involvement is important in family-based initiatives, the parent controls implementation of the treatment/intervention [32]. Thus, successful completion of program tasks is mostly determined by the parents’ motivation for participation [32]. Obesity prevention researchers have shown that parental motivation is significantly associated with encouragement of healthy behaviours (i.e. dietary and PA changes) in their children [32–34]. Therefore, it can be hypothesized that parental characteristics, particularly motivation to participate in and complete a behaviour change program with their child, are important in the development of obesity prevention initiatives for the family unit [32]. Thus, the researchers of the current paper have included measures to assess parental motivation to engage in healthy behaviours.

With regard to the most effective methods of targeting parents, Wolfenden and colleagues [21] reported that a random sample of parents of children between the ages of 2–15 expressed a preference for, and increased use of, low-intensity interventions, such as the delivery of information through mail or email. In addition, telephone and internet-based services were viewed as intensive and interactive support that parents would be most likely to use [21].

The research summarized above identifies a need for behaviour-based strategies to focus on modifying family lifestyle patterns to prevent and reduce the prevalence and impact of obesity and its associated health consequences on parents and their children. In order to promote behaviour change within the family unit, the method of education and/or Co-Active coaching was selected because of their success in developing sustainable behaviour change within individuals. The importance of considering empowerment when using parent-child dyads as a strategy to facilitate and sustain behaviour change has yet to be fully explored, and Co-Active coaching may prove to be an effective approach.

### Co-active coaching

Some coaching definitions and training programs posit that the primary purpose of coaching is to advise clients and is based on a relationship where the coach is viewed as the ‘expert’ [35]. In terms of health-related behaviour change, some studies consider a coach to be any support person who coaches an individual who is living with an illness of health issue [35]. However, coaching does not represent a specific phenomenon, but instead connotes a behavioural intervention with many dimensions and styles [35]. As such, it is important to clearly identify the method of coaching employed when attributing behaviour change to coaching [35].

Co-Active coaching [36] involves an alliance between coach and client, using key behavioural elements including self-efficacy, acknowledgement, goal-setting, personal values, and empowerment [36, 37]. The premise of Co-Active coaching does not center on solving problems, though problems may be solved through the process, but is a way of effectively empowering people to find their own answers [36]. The client is viewed as the expert on his/her own life and has the answers – albeit, often not concretized prior to coaching – to their own life questions, thus empowering the client to create their own solutions to their identified problems [36]. The term ‘Co-Active’ refers to the fundamental nature of a coaching relationship, in which the coach and client are active collaborators, and create an alliance in order to meet the client’s needs [38]. This partnership between coach and client seeks to meet the needs and learning style of the client, which, in turn, strengthens the client’s ability to self-manage his/her behaviours and attitudes based on his/her own values [36].

Co-Active coaching is an accredited coach-training method recognized by the International Coaching Federation [38]. The Co-Active coaching accreditation program spans approximately 12 months and is comprised of 5 in-person experiential workshops, followed by a six-month certification program [38]. The Coaches Training Institute [38] and Kimsey-House and colleagues [36] outline the three foundational principles of Co-Active coaching, which are: fulfillment (indicating life satisfaction); balance (based on using different perspectives to view situations and make meaningful choices); and process (fully experiencing any given moment). This Co-Active model is based on the client’s agenda, and the relationship between coach and client is tailored to the communication approach that works best for them [37–39].

### Co-active coaching and adult obesity

Researchers have established that interventions targeting health behaviour change should be based upon tested theories, and that these theories encompass the psychological and structural processes that are assumed to guide and regulate behaviour [40–42]. The Co-Active coaching approach has been grounded in several well-established behavioural theory frameworks [35, 39], such as Social Cognitive Theory [43], the Theory of Reasoned Action [41], and the Theory of Planned Behaviour [44]. Co-Active coaching researchers have demonstrated this approach’s effectiveness in producing positive behaviour change in a variety of health-related areas, such as PA, nutrition, and smoking cessation, and more germane to this study, overweight/obesity [45–48].

Co-Active coaching has been evaluated as an effective short- and long-term obesity reduction approach in adult populations, and shown positive results, including reductions in BMI and improvements in relevant psychosocial variables such as self-esteem and functional health status [47–49]. While an increasing number of studies have underscored the need to explore parent-focused or family-based childhood obesity prevention interventions [23, 28, 45, 50, 51], no studies have explored the utility of a coaching approach, such as Co-Active coaching, within a parent- or family-focused obesity reduction/healthy bodyweight promotion intervention aiming to impact both a parent and child concurrently. The value of coaching as a healthy weight intervention for adults, the necessity of incorporating parents in children’s health interventions (e.g., [52–55]), and supporting parent-child dyads is vital for sustained health behaviour change has been clearly outlined in previous research [18, 20, 22].

### Study purpose

This study will explore the impact of a parent coaching intervention, with parent and child outcomes, on promoting healthy behaviours among the dyad. Specifically, this research aims to identify the impact of a coaching plus health education intervention compared to health education only on: (a) the PA levels of children (ages 2.5–10) and their parents with overweight/obesity; (b) the dietary intake of children and their parents with overweight/obesity; (c) parental motivation to engage in healthy behaviours; and (d) parental perspectives on how the program has impact on their and their child’s nutrition and PA behaviours. These primary outcomes will be measured via in-person parent interviews, parent and child 7-day step count and 24 h dietary intake, and standardized and validated questionnaires. Due to children’s active growth periods, PA and nutrition behaviours can be better predictors of health than anthropometric indicators [54]. Secondary outcomes will be measured by assessing: (a) parental BMI (calculated by measuring weight in kg, over height in m^2^); (b) parents’ overall perception of health; and (c) parents’ psychosocial variables (i.e., social support, self-esteem, and self-efficacy).

The research team hypothesizes that immediately following and at 6 months post-intervention, the coaching plus education group will report higher levels of parent-child PA, greater improvements in parent-child dietary intake choices, greater parental psychosocial benefits, and greater improvements in parents’ BMI values, compared to those who receive education only. The research team predicts that parents from higher socioeconomic status (SES) backgrounds will be impacted more favorably than those from lower SES backgrounds, as researchers have found greater difficulties associated with affecting behaviour change within lower SES environments [20]. It is also hypothesized that male parents and children will have higher PA levels, while female parents and children will have greater dietary intake improvements, and female parents’ psychosocial health will be impacted most positively, given that previous research has found young males tend to be more active than their female counterparts, and obesity affects psychosocial health of women more negatively than men [27].

The purpose of the current protocol paper is to provide a detailed methodological account of this parent-child study with a view toward informing future coaching and obesity prevention/treatment programs designed to impact health behaviours positively within the family unit.

## Methods

### Study design

This 3-month, single centre, randomized controlled trial (in accordance with SPIRIT guidelines [56]) is currently underway and aims to improve PA and nutrition behaviours within the family unit. Using a single blind, block randomized design via computer randomization (using an online random sequence generator), parent-child dyads are assigned to either: coaching plus health education (intervention) or health education alone (control). The blocked randomization design ensures an equal proportion of dyads are assigned to each group. Only the lead researcher is aware of allocation assignment; parent participants are made aware of their group assignments at their baseline appointments.

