### Participants and recruitment

Ethical approval has been obtained from the Office of Research Ethics at the host institution. Participants are being recruited via poster advertisements at various locations including: clinics and medical offices, childcare centers, pharmacies, the local health unit, Young Men’s Christian Association (YMCA) sites, libraries, recreation centers, Ontario Early Years Centers, and community organizations (including local businesses). In addition, a radio advertisement is airing, and recruitment posters are advertised on Facebook groups/pages, Twitter, Kijiji, and in a local parenting magazine. Once participants contact the researcher, the study is explained in more detail, and the researcher asks several questions to determine eligibility. When a parent-child dyad is determined as eligible to participate, a baseline appointment is made in order to conduct the parent’s measurements (height, weight, and waist circumference), inform the parent of group assignment, sign consent forms, provide the dyad with pedometers, and further explain how the study will unfold.

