#### Data collection

Rolling enrollment has been adopted, making the data collection periods tailored to each individual in the study. Data are being collected at baseline (i.e., one week prior to the start of the intervention); six weeks into the intervention; immediately post-intervention (i.e., three months); and six months post-intervention. All data is being entered electronically at the host university, on a secure server. Consent and other written forms are stored and locked in a secure drawer, in a locked office, at the host university. In order to maintain confidentiality and anonymity, participants are assigned a unique identification code upon registering in the study. Participant files will be kept in storage for up to 5 years after completion of the study. Baseline and follow-up assessments are conducted at the host university or at the participant’s home by the lead researcher and a research assistant. An email link is sent to parent participants asking them to complete the questionnaires, and email and telephone reminders are conducted one and two weeks later if no response is received. If there is no response, it is assumed that the participant has missed the data collection time and contact re-commences at the next follow-up time. If a participant cannot be contacted after three consecutive communication attempts, it is assumed that they are lost-to-follow-up. A grocery store gift card is provided to participants who complete the study. An overview of study measurements and time points can be found in Table 1.

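### The design is called single blind, but no party is stated to be blind, and the arm is disclosed before the baseline step count and, as listed, before consent

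*Protocol article*

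**What the plan says.** The Study design section opens its account of allocation with "Using a single blind, block randomized design via computer randomization". It does not name the blinded party. It then states: "Only the lead researcher is aware of allocation assignment; parent participants are made aware of their group assignments at their baseline appointments".

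Under Data collection, baseline and follow-up assessments take place at the university or at the participant's "home by the lead researcher and a research assistant". How the two divide the tasks is not given.

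Under Participants and recruitment, callers are screened first: "the researcher asks several questions to determine eligibility". Eligible dyads are booked for a baseline appointment. Its purposes are listed in this order: the parent's height, weight and waist, then "inform the parent of group assignment, sign consent forms, provide the dyad with pedometers".

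The section on coaches has them deliver sessions to intervention parents only. The interview section has parents interviewed about the program at each follow-up. The Data analysis section makes baseline data the covariate in the between-group ANCOVA and has two independent researchers code the interviews.

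**The concern.** A report that says single blind tells its readers that a particular source of bias was closed off. Here the two parties usually meant by the term, the participant and the outcome assessor, are either told the arm or include someone who knows it.

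Three things are at stake.

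- **Assessment.** Parental BMI is a secondary outcome and the subject of a stated hypothesis, and the interviews are counted among the primary outcomes. Both are open to influence from an assessor or interviewer who knows the arm.
- **Entry to the trial.** If the arm is announced before consent is signed, a parent who dislikes it can withdraw unsigned. The two arms may then differ in the motivation of those who remain.
- **Baseline.** A baseline value collected after the parent knows the arm is no longer a pre-assignment value, yet the analysis adjusts for it as if it were.

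**Working it through.** The plan gives no figure for blinding or concealment. Its power statement (79% for 50 dyads, d = 0.8, alpha 0.05) reproduces at 0.791 with a two-sided t-test and 25 per arm, but does not enter this point. The check is a comparison of sections.

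**Step 1. Who could be the blinded party?**

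| Party | What the article states | Blind? |
|---|---|---|
| Parents | Told their arm at the baseline appointment | No |
| Coaches | Deliver coaching to intervention parents only | No, by role |
| Lead researcher | Knows the allocation; is one of two assessors | No |
| Research assistant | The other assessor; knowledge of the arm not mentioned | Possible, not stated |
| Interviewer | Not identified; the topic is the parent's experience of the program | Not stated; content likely to reveal the arm |
| Transcript coders | Two independent researchers | Not stated |

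Nobody is stated to be blind. The one assessor who might be shares the work with one who is not.

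**Step 2. Order of events at the baseline appointment.** The listed order is body measurements, disclosure of the arm, consent, pedometers. Two consequences follow, and they differ in strength.

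- Refusal after disclosure depends on the list being chronological. The article does not say that it is.
- Step counts collected with the arm known do not depend on the order within the visit. The pedometer is handed over at the same appointment at which the arm is announced, and it is then worn for seven days. The baseline week therefore follows disclosure in any case.

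**Step 3. What this does to the adjusted comparison.** With coaching arm C and education arm E, the ANCOVA estimate is

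adjusted difference = (mean follow-up C − mean follow-up E) − b × (mean baseline C − mean baseline E),

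where b is the within-arm slope of follow-up on baseline. Suppose that learning the arm shifts the baseline step count by δ on average in C relative to E and leaves follow-up unchanged. The estimate then moves by −b × δ. With b positive, coached parents who start walking more in the baseline week (δ > 0) make coaching look less effective, and a shift the other way makes it look more effective. The article gives neither b nor δ, so no number can be attached. The term does not shrink with more dyads.

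**Step 4. Where an assessor's knowledge can reach.** Questionnaires go out by email link, the diet recall is online, and steps are counted on a pedometer worn by the participant. That leaves height, weight, waist and the interviews.

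**The case against.** Several stronger conclusions are tempting, and the document does not carry them.

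- **That allocation is not concealed.** The article does not say how the sequence is held, who can see it, or what the block size is. It says that a researcher screens callers, without identifying that person as the lead researcher. A journal article may leave such detail to the full protocol. Telling parents their arm after assignment is a matter of blinding and does not by itself show that the sequence was visible beforehand. Any argument that someone could foresee the next assignment is conditional on facts not given.
- **That nobody is blind.** Read literally, the statement that only the lead researcher knows leaves the research assistant unaware. That may be what the authors meant. It remains true that the article does not say so, gives the assistant sole charge of no measurement, and has parents discuss the program at every follow-up.
- **That the allocation sentence contradicts itself.** An ordinary reading is that only the lead researcher knows until the baseline appointment, when parents are told. On that reading the sentence describes the time before disclosure and still does not say who is blind afterwards.
- **That the lead researcher personally takes the measurements or runs the interviews.** The article names two assessors without dividing their tasks and does not name the interviewer.

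The reach of assessor bias is also limited: BMI is secondary, the eligibility criteria are largely factual, and interviews are recorded, transcribed verbatim and coded by two people. All of this stands and narrows the point. It does not supply a blinded party for the label, and it does not move the baseline step week ahead of disclosure.

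**Conclusion.** The point holds in a limited form and should be corrected. The label single blind is not supported by the procedures described: parents, coaches and one of two assessors know the arm, and no one else is stated not to. Allocation concealment is not assured as described, because disclosure is listed before consent; that it failed is not shown. The baseline step count is collected after disclosure, on the article's own account of when pedometers are handed out.

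The size of any resulting bias cannot be estimated from the document, and its direction for the step count is unknown. The consent part rests on reading the list of visit tasks as a sequence. The blinding part rests only on what the article says about who knows and who assesses. Nothing here invalidates the randomization; the defect is a claimed protection that the described procedures do not deliver.

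**What to change.** For dyads not yet enrolled and visits not yet held:

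1. Release each assignment only after written consent and completion of all baseline measures, including the seven-day step count and the questionnaires.
2. Have the existing research assistant, who is not told the arm, take follow-up height, weight and waist before the interview begins.
3. Mask the arm in interview transcripts before coding, where the content allows.
4. Replace the label with a plain statement: participants and coaches not blinded; assessor of anthropometric outcomes blinded. Say in the report who held the sequence and who screened.

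If steps 1 and 2 are not adopted, delete single blind. For dyads already enrolled, accurate description is all that remains possible.

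The cost is a reallocation of tasks among existing staff and a change of wording. Disclosure of the arm moves to a later contact. Some unmasking of the assistant will still occur, because parents may mention coaching. Procedures will differ between earlier and later dyads, so the date of the change should be recorded and reported.
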